##### Food frequency questionnaire (FFQ)

2.5.1.2

A validated, child-specific FFQ (23) will assess habitual diet over the past month at baseline (T0), post-intervention at 3 months (T1), and at 6-month follow-up (T2, 9 months), including 65 items across 11 food categories. The frequency and portion sizes of coarse cereals, sugar-sweetened beverages, and snacks will be recorded.

#### Outcome indicators

2.5.2

Primary outcomes will be selected to assess the direct effect of increased coarse-cereal intake on overweight and obesity. Secondary outcomes, including indicators related to metabolism and gut microbiota, will be measured at baseline (T0) and at the end of the intervention (T1, 3 months).

##### Primary outcome indicators

2.5.2.1

(1) Body Mass Index (BMI)

Height and weight will be measured using a calibrate stadiometer and digital scale, with students in light clothing and barefoot after fasting. BMI will be calculated as weight (kg)/ height^2^ (m^2^) and categorized according to Chinese reference standards.

(2) Body Composition

Measured using an 8-electrode, 4-frequency bioelectrical impedance analyzer (InBody 770, Biospace Co., Ltd.) validated for children to assess body fat and lean mass.

(3) Waist Circumference (WC)

Measured at the midpoint between the lowest rib and iliac crest with a non-elastic tape, in triplicate, to 0.1 cm accuracy.

(4) Blood Pressure (BP)

Measured using an electronic sphygmomanometer (HBP-1300, Omron) after 5 min of rest; two readings will be taken with a 3-min interval. Childhood obesity is a significant risk factor for elevated blood pressure, which serves as a sentinel indicator for assessing cardiometabolic risk. By incorporating blood pressure measurements, this study aims to investigate whether increasing dietary fiber intake through coarse-cereal consumption offers potential benefits in improving early cardiovascular risk markers associated with obesity.

##### Secondary outcome indicators

2.5.2.2

(1) Metabolic Indicators

After an 8–10 h overnight fast, 5 mL of venous blood will be collected from 200 overweight/ obese students. Serum will be centrifuged and stored at −80 °C.

(2) Carbohydrate metabolism

Fasting blood glucose (FBG), fasting insulin (FI), and insulin-like growth factor 1 (IGF-1) will be assessed.

(3) Lipid metabolism

Lipid profile (enzymatic colorimetric method) and adipokines (leptin, leptin receptor, adiponectin via ELISA) will be measured. Serum uric acid (SUA) will be also assessed.

(4) Gut Microbiota

Forty overweight/ obese students per group provided ~5 g fecal samples at T0 and T1, stored at −80 °C. 16S rRNA V4-V5 sequencing will be performed to assess alpha diversity (Shannon index), beta diversity (Bray-Curtis distance), and relative abundance of fiber-degrading bacteria (e.g., *Bifidobacterium, Akkermansia*).

#### Dietary behavior-associated indicators

2.5.3

Satiety index (SI) will be assessed on 2 working days via a 10-point scale after breakfast and lunch.

#### Influencing indicators

2.5.4

Potential confounders will be measured and adjusted in analysis:

(1) Physical Activity and Sedentary Behavior

Students will wear smart wristbands for 7 consecutive days (including 5 school days and 2 weekend days) at baseline (T0) and at the end of the 3-month intervention (T1) to measure activity duration and frequency, sedentary time, and sleep.

(2) Dietary Preference and Cognition

Dietary preferences, knowledge, and home environment will be assessed using a structured questionnaire developed for this study. The questionnaire items were generated based on a literature review and expert consultation (involving pediatric nutritionists and epidemiologists), and its face validity was confirmed through pilot testing with a small group of non-participant students and parents for clarity and comprehension. It assessed preference for coarse cereals, ability to identify coarse-cereal foods, snacks choices, parental home coarse-cereal availability, cooking frequency, and role modeling (23).

(3) Baseline Demographic

Age, sex, family information, and other health data.

### Statistical analysis

2.6

Analysis accounts for the cluster-randomization design, with schools as clusters and students nested within schools. Intention-to-treat (ITT) principles are applied, using SAS 9.4.

#### Descriptive statistics and baseline comparison

2.6.1

Continuous variables are presented as mean±standard deviation (SD) or median (skewed). Normality will be tested via Shapiro–Wilk test and Q-Q plots. Categorical variables are summarized as counts (%). Baseline differences will be assessed using t-tests or Mann–Whitney U tests for continuous variables, and χ^2^or Fisher’s exact tests for categorical variables.

#### Outcome analysis

2.6.2

Analysis will be performed following the intention-to-treat principle. Mixed-effects linear models (MLMs) will be used to evaluate changes in outcomes from baseline (T0) to post-intervention (T1) and follow-up (T2). The models will include group (intervention/control), time (T1, T2), and the group-by-time interaction as fixed effects, with the baseline value (T0) of the respective outcome included as a covariate. Individual-level intercepts will be fitted as random effects to account for repeated measurements, and school will be included as a random effect to adjust for the cluster-randomized design. The models will be further adjusted for prespecified covariates, including age, sex, and baseline physical activity level. The primary test for intervention effect will be the significance of the group-by-time interaction term.

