### Data collection

2.5

Data will be collected at three time points: baseline (T0), post-intervention at 3 months (T1), and at 6-month follow-up (T2, 9 months). The specific time points for each category of data collection are detailed in Figure 2.

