#### Subgroup and sensitivity analyses

2.6.3

Pre-specified subgroups included se and baseline BMI category. Three way interactions (group x time x subgroup) tested effect modification, with Bonferroni correction (*α* = 0.025). Per-protocol analysis excluded participants with <50% intervention adherence. Complete-case analysis will be conducted to assess robustness to missing data.

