### Limitations

3.4

Several limitations should be considered within the context of this pragmatic design. First, the 3-month intervention period may not capture long-term effects, although the 6-month follow-up provides a partial evaluation of maintenance. Second, as a pilot pragmatic cluster-randomized trial (pRCT) conducted in only two primary schools in suburban Beijing, the findings are primarily applicable to similar settings with on-site cafeterias. While the limited number of clusters may increase the risk of baseline imbalance, this pilot scale was necessary to test the feasibility and implementation fidelity of the intervention before wider rollout. Third, consistent with the nature of pragmatic trials conducted in real-world settings, blinding of participants and school staff was not feasible. Although this introduces the potential for performance bias, it reflects the actual conditions under which such dietary interventions would be implemented. To mitigate detection bias, we strictly maintained blinding of outcome assessors for anthropometric and biological measurements. Finally, unmeasured confounders, such as family lifestyle factors not captured in current assessments, may influence outcomes, a challenge common to school-based community interventions.

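### The named primary test, group-by-time with time limited to T1 and T2 and baseline as a covariate, measures the change in the group difference between T1 and T2, not the intervention effect

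*Protocol article*

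**What the plan says.** Section 2.6.2 (Outcome analysis) says that mixed-effects linear models are to "evaluate changes in outcomes from baseline (T0) to post-intervention (T1) and follow-up (T2"). It then sets out the model:

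- Fixed effects: "The models will include group (intervention/control), time (T1, T2), and the group-by-time interaction as fixed effects".
- Baseline: "with the baseline value (T0) of the respective outcome included as a covariate".
- Random effects: an individual intercept, and "school will be included as a random effect to adjust for the cluster-randomized design".
- Decision rule: "The primary test for intervention effect will be the significance of the group-by-time interaction term".

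No group main effect, visit-specific contrast, averaged contrast or joint test is named as primary.

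For subgroups, section 2.6.3 says: "Three way interactions (group x time x subgroup) tested effect modification".

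Section 2.5 places the visits after baseline as "post-intervention at 3 months (T1), and at 6-month follow-up (T2, 9 months"). The Limitations (section 3.4) say that "the 6-month follow-up provides a partial evaluation of maintenance".

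**The concern.** A group-by-time term measures a treatment effect when baseline is one of the levels of time, because it then compares the two groups' changes from baseline. Here baseline has been moved to the right-hand side of the model and only T1 and T2 remain as outcomes. The interaction then compares the groups on what happens between T1 and T2. The group difference that already exists at T1 sits in the group coefficient, which the plan does not name as the test.

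The rule that decides the trial's conclusion is therefore aimed at a different question from the stated one, which is change from T0 to each later visit. It also sits badly with the stated purpose of the follow-up: an effect that is fully maintained is the pattern to which this test is blind.

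**Working it through.** **1. What the term estimates.** Let G = 1 for intervention, L = 1 for T2 and 0 for T1, and Y0 the baseline value. The model in section 2.6.2, apart from further covariates and random effects, is

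Y = b0 + b1·G + b2·L + b3·G·L + c·Y0.

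- Adjusted group difference at T1: d1 = b1.
- Adjusted group difference at T2: d2 = b1 + b3.
- Hence b3 = d2 − d1.

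If d1 = d2, the true b3 is 0 for any size of d1. This step needs no numerical assumption.

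**2. The two readings that would rescue the rule.**

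- If T0 were a level of time, the interaction terms would be differences in change from baseline. The text lists the levels as T1 and T2 and gives T0 the role of covariate.
- If the model had no separate group term, the group-by-time terms would be the visit-specific effects d1 and d2. The text lists group as its own fixed effect.

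**3. Inputs for the size of the problem.** From section 2.3.1: SD 1.39, difference 0.17, two-sided alpha 0.05, 180 students per school. The protocol gives no between-visit correlations, so those below are assumptions. No school effect is assumed.

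The 180 is borrowed only as the plan's own input. It is not reproduced by the usual formula: 2 × (1.96 + 0.8416)² × 1.39² / 0.17² gives 1,050 per arm before any design effect. That is a separate matter, and nothing here depends on it.

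**4. Formulas.** With complete data at T1 and T2 and a random individual intercept, b3 equals the between-group difference in mean (T2 − T1). One simulated data set confirmed this: the mixed model and the two-sample comparison both gave −0.02345 (p = 0.617 and 0.618). With r the T1–T2 correlation in the first formula and the T0–T1 correlation in the second:

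- SE of the interaction = √(2 × 2 × 1.39² × (1 − r) / 180)
- SE of the T1 contrast adjusted for baseline = √(2 × 1.39² × (1 − r²) / 180)

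| r | SE, interaction | Power if −0.17 at T1 and 0 at T2 | SE, T1 contrast | Power of T1 contrast for −0.17 |
|---|---|---|---|---|
| 0.80 | 0.0927 | 45% | 0.0879 | 49% |
| 0.90 | 0.0655 | 74% | 0.0639 | 76% |
| 0.95 | 0.0463 | 96% | 0.0458 | 96% |

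Example at r = 0.95: 0.17 / 0.0463 = 3.67, and Φ(3.67 − 1.96) = Φ(1.71) = 0.956.

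**5. Simulation (4,000 runs per scenario, 180 per arm).** Effect of −0.17 at both T1 and T2:

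| Correlations T0–T1 / T0–T2 / T1–T2 | Planned interaction | T1 contrast | Mean of T1 and T2 |
|---|---|---|---|
| 0.80 / 0.70 / 0.80 | 5.1% | 47.8% | 49.9% |
| 0.90 / 0.85 / 0.90 | 4.9% | 74.6% | 77.1% |
| 0.95 / 0.90 / 0.95 | 5.6% | 95.6% | 90.6% |

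Doubling the effect to −0.34 at both visits (last correlation set) leaves the interaction at 5.0% and takes both contrasts to 100%.

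Other patterns, last correlation set, planned interaction:

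- Effect lost by T2 (−0.17, then 0): significant in 95.7% of runs.
- Effect half lost (−0.17, then −0.085): 46.0%.
- Effect only at T2 (0, then −0.17): 96.0%.

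**6. Subgroups.** By the same algebra, the three-way term in section 2.6.3 is the subgroup difference in (d2 − d1). It does not test whether d1 or d2 differs by subgroup.

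**7. A consistency check.** Section 2.5.2 measures the metabolic and microbiota outcomes only at T0 and T1. With T0 as a covariate, time then has one level and no group-by-time term exists for these outcomes.

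**The case against.** The strongest reply is that this is loose drafting. The section speaks of change from T0 and calls the interaction the test of the intervention effect. Both fit the usual model with T0 among the outcomes, where T1 and T2 would be the two non-reference terms. The slip would then be only that T0 is also entered as a covariate. This is possible but is the weaker reading, because the same sentence lists all the levels of group and so presumably all the levels of time. Either way the section must be changed.

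Three further points stand and limit the claim.

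- A reader might infer that any real, lasting effect would be declared null. The documents do not support that. Rejection falls to alpha only when the effects at T1 and T2 are equal. A half-lost effect reached significance in 46% of runs at the highest correlations, though as evidence of fading.
- A reader might also infer that a lost benefit will certainly give a positive result, or that a positive result means the benefit vanished. Neither follows. At a T1–T2 correlation of 0.80, complete loss is detected in about 45% of trials, and late emergence also produces significance.
- A reader might infer that a T1 contrast would restore a sound test at the quoted power. It would not. Section 2.2 randomises two schools, one per arm, so a group contrast has no between-school degrees of freedom. A constant difference between the schools cancels from the planned interaction, but baseline adjustment removes only part of it from a T1 contrast.

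**Conclusion.** The point holds as a matter of model structure. As section 2.6.2 is written, the named primary test estimates the change in the group difference from T1 to T2. For an effect equal at both visits it has power equal to alpha, about 5%, at any effect size and any between-visit correlation. A significant result reflects fading, growth or late emergence. The subgroup test in section 2.6.3 shares the defect.

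The zero interaction rests on nothing beyond the stated model. The powers of the alternative contrast (about 47%, 75% and 96%) rest on assumed T0–T1 correlations of 0.80, 0.90 and 0.95, on the plan's SD, difference and 180 per arm, and on no school effect, so they are upper bounds. This is an error in what the article fixes, not a detail left to an analysis plan, and it should be corrected before outcomes are analysed.

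**What to change.** In section 2.6.2, replace the sentence naming the primary test with one of these:

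1. Keep T0 as a covariate and name the baseline-adjusted between-group contrast in BMI-SDS, either at a stated visit or averaged over T1 and T2. If T1 is chosen, the T2 contrast becomes the test of maintenance.
2. Make T0 a level of time, drop it as a covariate, and name the T0-to-visit contrast.

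In either case, report the group-by-time change from T1 to T2 only as a description of fade or growth. In section 2.6.3, test effect modification with group-by-subgroup at the same visit.

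Before naming the visit, reconcile the timing. The Abstract gives assessments at 3 and 6 months, section 2.4.3.3 refers to a 6-month intervention period, and section 2.5 puts T1 at 3 months and T2 at 9 months. If T1 is confirmed as the end of the intervention, it is the natural primary visit.

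Add a statement that with one school per arm any such contrast is confounded with school, that the school random effect cannot separate the two, and that the p-value and confidence interval are therefore conditional on no school effect. Under option 2 a constant difference between the schools cancels, but a school-specific change over time does not.

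The cost is a sentence or two in each of sections 2.6.2 and 2.6.3 and one contrast statement in SAS. No new data are needed. The change does not cure the confounding with school.

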#### Subgroup and sensitivity analyses

2.6.3

Pre-specified subgroups included se and baseline BMI category. Three way interactions (group x time x subgroup) tested effect modification, with Bonferroni correction (*α* = 0.025). Per-protocol analysis excluded participants with <50% intervention adherence. Complete-case analysis will be conducted to assess robustness to missing data.

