**Methods:**

A two-arm pragmatic cluster-RCT will be conducted in public primary schools in Huairou District, Beijing. Two schools will be randomly assigned to intervention or control groups, with 400 students (grades 3–4, aged 8–12 years) enrolled. The intervention group will receive a daily 50 g coarse-cereal substitution in school meals, aligned with Chinese dietary guidelines, alongside a multi-level nutrition education program targeting students, parents, and school staff. The control group will continue standard practices. Primary outcomes include changes in body mass index standard deviation score (BMI-SDS), body composition, waist circumference, and blood pressure, assessed at baseline, 3 months, and 6 months. Secondary outcomes encompass metabolic indicators and gut microbiota profiles in overweight/obese subgroups. Data will be analyzed using mixed-effects linear models, accounting for cluster effects. Implementation fidelity will be monitored through quantitative and qualitative methods.

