### Randomization and allocation

2.2

Clusters, defined as individual schools, serve as the unit of randomization. The study population is drawn from public primary schools in Huairou District, Beijing, where the prevalence of overweight and obesity among school-aged children exceeds 30%, highlighting the need for effective interventions.

Eligible schools met the following criteria: (1) Availability of an on-site cafeteria capable of providing daily breakfast and lunch to ensure consistent implementation of coarse-cereal substitution; (2) No dietary intervention programs implemented in the past year; (3) Enrollment of at least 150 students in grades 3–4 (ages 8–12) to ensure sufficient sample size per cluster, and (4) Approval from school administrators to participate in the trial.

Two schools meeting these criteria will be randomly assigned to either the intervention or control group using a computer-generated random number table (SAS 9.4).

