### Future directions and practical applications

3.3

To evaluate long-term effects, future studies should extend intervention and follow-up periods to 12 months, enabling assessment of sustained coarse-cereal consumption and obesity prevention. Assessing the feasibility of independent school-based provision after the intervention is critical. Adaptation for rural schools, where on-site cafeterias are often absent, may involve pre-packaged coarse-cereal snacks or parent-led meal preparation while maintaining the 50 g daily target. These strategies could reduce rural–urban disparities in childhood obesity and align with China’s Rural Compulsory Education Student Nutrition Improvement Program.

Subgroup analyses by gender and baseline weight status could refine intervention targeting, focusing on high-risk populations if differential efficacy is observed. Linking gut microbiota changes to metabolic outcomes, such as insulin sensitivity and lipid profiles, may support development of microbiome-informed, personalized interventions.

If proven effective, the findings and resources from this study are intended to inform practical applications and policy. The standardized resources developed, including the recipe library, digital monitoring tools, and staff training protocols, could be consolidated into a “Coarse-Cereal School Toolkit” for broader adoption. The toolkit would provide a tangible pathway for integrating coarse cereals into national policies, such as an update to the Nutritional Guidelines for Student Meals (24), potentially mandating or strongly recommending the inclusion of coarse cereals in school meal programs.

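### Effect modification by baseline weight is tested on BMI categories although baseline BMI-SDS is measured; for a graded effect this discards about 16–42% of the interaction information

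*Protocol article*

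**What the plan says.** Section 2.6.3 (Subgroup and sensitivity analyses) states: "Pre-specified subgroups included se and baseline BMI category". The first factor, printed with a letter missing, is read here as sex; section 3.3 refers to gender. The test is described as "Three way interactions (group x time x subgroup) tested effect modification", "with Bonferroni correction" to an alpha of 0.025, which is 0.05 divided by the two factors.

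Section 2.5.2.1 says that BMI is "categorized according to Chinese reference standards". It gives neither the number of categories nor the cut-offs. The abstract lists BMI-SDS among the primary outcomes and has it assessed at baseline, and section 2.3.1 sizes the trial on it. Section 2.6.2 enters the baseline value of each outcome as a covariate only, without an interaction with group.

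Section 3.3 gives the analysis a purpose: "Subgroup analyses by gender and baseline weight status could refine intervention targeting, focusing on high-risk populations if differential efficacy is observed".

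**The concern.** The trial records a continuous modifier and then tests a coarser version of it. Categories treat all children within a band as alike and separate children who sit just either side of a cut-off. With three or four bands, the test is also spread over two or three degrees of freedom instead of one. If the benefit rises or falls steadily with baseline weight, all of this costs sensitivity.

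What is at stake is the targeting question in section 3.3. A less sensitive test makes it harder to learn whether heavier children respond differently, although the better modifier costs nothing extra to use.

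**Working it through.** The protocol gives no power or sample size for any interaction, so there is no stated figure to reproduce. The check compares the two codings.

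**Inputs from the documents.** Alpha is 0.025 (2.6.3). SD is 1.39 and the difference 0.17 (2.3.1). There are 180–200 children per arm, so 360–400 in all (2.3, 2.3.1). Section 2.2 describes a district "where the prevalence of overweight and obesity among school-aged children exceeds 30" per cent. Section 2.5.2.2 plans blood samples from 200 overweight or obese students; if all are among the 400 enrolled, that implies a share of about 50%.

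**Assumptions.** Baseline BMI-SDS is roughly normal, arms are equal, and modification is linear. There are two to four categories. Overweight and obese are equally frequent, and a fourth (lowest) band holds 5%.

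**Step 1: information kept.** For a standard normal modifier cut into bands with shares p_k and band means m_k, the share kept is the sum of p_k × m_k². For two bands split 70/30 this is φ(0.524)² / (0.70 × 0.30) = 0.3477² / 0.21 = 0.576.

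**Step 2: power.** A continuous 1-df test has 80% power at alpha 0.025 when the non-centrality is (2.241 + 0.842)² ≈ 9.505. This is multiplied by the share kept, and power is read from the non-central chi-square on (number of bands − 1) df.

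| Split | Kept | Lost | Non-centrality | df | Power |
|---|---|---|---|---|---|
| 70/30 | 0.576 | 42% | 5.47 | 1 | 54% |
| 70/15/15 | 0.623 | 38% | 5.92 | 2 | 47% |
| 5/65/15/15 | 0.755 | 25% | 7.17 | 3 | 49% |
| 50/50 | 0.637 | 36% | 6.05 | 1 | 59% |
| 50/25/25 | 0.749 | 25% | 7.12 | 2 | 56% |
| 5/45/25/25 | 0.838 | 16% | 7.96 | 3 | 54% |

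The loss is therefore 16–42%, and the 80% benchmark becomes 47–59%. Testing both follow-up visits jointly at the 30% share gives 44–52%, so the choice of group term changes little.

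**Step 3: power on the protocol's own inputs.** With clustering ignored, the standard error of the interaction per SD of baseline is 2 × 1.39 / √N: 0.147 at N = 360 and 0.139 at N = 400. A continuous test reaches 80% power only if the effect changes by 3.083 × 0.147 = 0.45 or 3.083 × 0.139 = 0.43 BMI-SDS per SD of baseline. That is more than 2.5 times the whole assumed effect of 0.17. If the effect changed by a full 0.17 per SD, the non-centrality would be 1.35–1.50. Power would then be about 14–15% continuous and about 7–10% with categories. Baseline adjustment would reduce the SD of 1.39 by an amount that the documents do not give, so these figures are indicative.

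**Step 4: other shapes, at the 30% share.** For a smooth S-shape centred on the cut-off, a linear term with 80% power compares with 80%, 73% and 67% for two, three and four bands. For a pure step at the cut-off the order reverses: 80% for two bands against 54% for the linear term.

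**Step 5: Holm.** Suppose both interactions are real, independent and have 50% power at 0.025. Each then has 61.1% power at 0.05. Holm gives 0.50 + 0.50 × (0.611 − 0.50) = 0.555, against 0.50 for Bonferroni, at the same family-wise error rate.

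**The case against.** The strongest objection is that weight-status groups suit a question about targeting weight-status groups. They follow a national reference, and the metabolic and microbiota outcomes are already confined to overweight or obese children. This justifies showing results by category. It does not make categories the better test, unless the effect really jumps at the cut-off; in that case the objection stands.

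It is also fair that normality, linearity, the number of bands and their split are assumed, and that a condensed article may leave knots and display to a fuller plan. The modifier itself, however, is stated in section 2.6.3 and is not left open.

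With one school per arm, any interaction between group and baseline weight is also one between school and baseline weight. A sharper test would pick up school differences just as readily. This stands, and recoding does not cure it. Bonferroni at 0.025 is valid, so Holm is only a small gain.

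A reader might infer three stronger things that the documents do not support:

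- **That the coding cuts this trial's interaction power from 80% to about half.** The 80% in section 2.3.1 belongs to the main effect. Step 3 shows that both codings would usually miss a plausible gradient, so coding is not the main reason for missing one.
- **That the upper categories are sparse, at 54–60 children per arm (30% of 180–200).** Section 2.2 gives a district figure and only a lower bound, while section 2.5.2.2 points to as much as half the sample.
- **That a null test will be reported as an equal effect across weight status.** No section says so.

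**Conclusion.** The point holds as one of efficiency. The plan tests a coarser modifier than the one it measures, and under graded modification that gives up roughly a sixth to two-fifths of the interaction information. This depends on a roughly normal BMI-SDS, a linear effect, two to four bands and a 30–50% overweight or obese share. The size of the loss is relative: it compares two codings and does not predict this trial's power. Because the analysis is secondary and weakly powered in any case, this is a cheap improvement and not a flaw that threatens the main result.

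**What to change.** In section 2.6.3:

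- Name continuous baseline BMI-SDS as the tested modifier, with its main effect in the model. It must be added for outcomes other than BMI-SDS, where section 2.6.2 supplies only that outcome's own baseline.
- Report the group difference with its confidence interval at stated BMI-SDS values, for example 0, 1 and 2.
- Check non-linearity once, with a three-knot restricted cubic spline.
- Keep the category-specific estimates as a descriptive table.
- Replace Bonferroni with Holm across the two modifiers.

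The cost is a few sentences of wording, with no new data, staff or participants. The one downside is less power if the effect is a true step at the reference cut-off; the spline check and the retained table would help to reveal that.

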#### Sample size calculation

2.3.1

The primary outcome for sample size estimation was the Body Mass Index Standard Deviation Score (BMI-SDS). Due to the lack of previous studies on coarse-cereal interventions in this population, sample size was estimated based on prior research evaluating comprehensive interventions on obesity in primary school students. The calculations assumed 80% power (*β* = 0.20), a two-sided significance level of 0.05 (*α* = 0.05), standard deviation *σ* = 1.39, and effect size *Δ* 0.17. The resulting sample size was 180 students per school. Allowing for 10–20% attrition, the target enrollment per school was set at 190–200 students (18). The calculation formula used will be:

$$n=\frac{{\left(Z_{\alpha /2}+Z_{\beta }\right)}^{2}{\left(2\sigma^{2}\right)}^{2}[1+(m-1)\rho ]}{{\left(\mu_{1}-\mu_{2}\right)}^{2}}$$

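### The one named check on missing data, a complete-case analysis, uses a subset of the mixed model's data under a stronger assumption and cannot show robustness to informative dropout

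*Protocol article*

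**What the plan says.** Section 2.6.2 (Outcome analysis) sets the primary analysis. It opens with "Analysis will be performed following the intention-to-treat principle" and specifies a linear mixed model. The fixed effects include group, "time (T1, T2), and the group-by-time interaction as fixed effects", "with the baseline value (T0) of the respective outcome included as a covariate". For the within-child structure, "Individual-level intercepts will be fitted as random effects to account for repeated measurements". Baseline is therefore a covariate, and only T1 and T2 are outcome rows.

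Section 2.6.3 (Subgroup and sensitivity analyses) then names the check on missing data and gives its purpose: "Complete-case analysis will be conducted to assess robustness to missing data". The other sensitivity analysis there concerns adherence: "Per-protocol analysis excluded participants with <50% intervention adherence". Section 2.7 lists attrition rates at T1 and T2 as an implementation metric and compares high with low adherers. Neither re-estimates the intervention effect under a different assumption about missing outcomes.

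Section 2.3.1 (Sample size calculation) expects losses: "Allowing for 10–20% attrition, the target enrollment per school was set at 190–200 students". It takes a BMI-SDS difference of 0.17 and an SD of 1.39.

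**The concern.** A sensitivity analysis for missing data should vary the assumption on which the primary analysis depends. For a likelihood-based mixed model, that assumption is missing at random: given baseline, group, covariates and any outcome already observed, missingness does not depend on the unseen value. A complete-case analysis does not relax this. It discards the children with one post-baseline value and requires missingness to be unrelated to the outcomes given the covariates alone. The check is thus valid under fewer mechanisms than the analysis it is meant to test.

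The matter is relevant here because students, parents and staff know the allocation (section 2.1), the outcomes are weight-related, follow-up runs to 9 months (section 2.5) and the target difference is small. Losses tied to how a child's BMI-SDS changed, differing between the two schools, are plausible, though the documents do not show that they will occur. If they did, the planned check could agree with the primary result without telling the reader that both were biased.

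**Working it through.** The article gives no figure for this point, so there is none to reproduce. The check has three parts.

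**1. Which children enter each analysis (missing outcomes only)**

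| Child's T1/T2 data | Mixed model, all available visits | Complete-case |
|---|---|---|
| Both visits | used | used |
| One visit only | used | dropped |
| Neither visit | no outcome to contribute | dropped |

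The two differ only in the middle row. If every loss occurs before T1 and is permanent, that row is empty, the data sets are identical and the estimates agree by construction, whatever the reason for the loss.

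**2. Simulation of the comparison**

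From the article: 200 per arm, BMI-SDS SD 1.39, true effect −0.17 at T1 and T2, and dropout of about 20% per arm (the top of the stated range). Assumed: change from baseline with between-child SD 0.35 and residual SD 0.20; logistic dropout in the intervention arm, with 20% random dropout in controls (in the first row, 20% random in both arms); no school effect. There were 400 replicates (Monte Carlo SE about 0.002).

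| Dropout mechanism | Mixed model T1 / T2 | Complete-case T1 / T2 |
|---|---|---|
| Completely at random, before T2 | −0.168 / −0.169 | −0.167 / −0.168 |
| Depends on observed T1 | −0.170 / −0.171 | −0.264 / −0.242 |
| Depends on unseen T2 | −0.170 / −0.212 | −0.241 / −0.265 |
| Depends on unseen T1, lost before T1 | −0.263 / −0.239 | −0.263 / −0.239 |

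- Row 2: the primary model is right and the check is wrong by 0.07–0.09.
- Row 3: at T2 both are wrong. A gap appears, as in row 2, so a gap does not tell the two mechanisms apart.
- Row 4: both are wrong and agree exactly.

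The sizes depend on the assumed SDs and dropout models. The exact agreement in row 4 does not.

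**3. Size of the possible bias**

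Let p be the missing fraction and delta the amount by which missing intervention children are worse in BMI-SDS than the model predicts, with missing controls as predicted. The intervention mean is then understated by p × delta, so the bias in the group difference is p × delta in favour of the intervention.

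| p | delta | Bias | Share of 0.17 |
|---|---|---|---|
| 0.10 | 0.2 | 0.02 | 0.02/0.17 = 12% |
| 0.20 | 0.2 | 0.04 | 0.04/0.17 = 24% |
| 0.10 | 0.5 | 0.05 | 0.05/0.17 = 29% |
| 0.20 | 0.5 | 0.10 | 0.10/0.17 = 59% |

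The 10–20% range is the article's. Delta has no source in it and is an assumption. Under the simulation's SDs, the SD of BMI-SDS given baseline is √(0.35² + 0.20²) ≈ 0.40, so a delta of 0.5 is about 1.24 SD for every missing child. It is an adverse extreme, not an expectation. To account for the whole 0.17 at 20% missing, delta would have to be 0.17/0.20 = 0.85.

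**The case against.** The strongest reply is that this is a condensed article and the full plan is not shown. Complete-case analysis is a common supplement, the sentence does not claim to test for informative dropout, and analyses that allow for it are often left to the SAP. Part of this stands: a reader might infer that the trial plans no such analysis, and the article cannot support that. What remains is that the article names a method, assigns it the purpose of assessing robustness, and the method is poorly suited to that purpose.

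A second reply is that the comparator is assumed. Section 2.6.2 does not say that all available visits are used, or that data are taken as missing at random. The model also adjusts for baseline physical activity, and a child without that value would drop out unless it is imputed. With missing covariates, complete-case analysis does not always need the stronger assumption. This stands as a limit: the point concerns missing outcomes and a likelihood fit to available visits.

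Three stronger readings are tempting and are not supported:

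- A reader might infer that a gap between the analyses points to a fault in the complete-case set alone. Row 3 of the simulation shows otherwise: at T2 both are biased. A gap does carry some information, namely that dropout is not completely at random.
- A reader might infer that heavier children avoiding re-measurement would by itself bias the result. The model conditions on baseline value and group, so dropout driven by baseline BMI-SDS is handled even when it differs by arm. With the same assumed SDs and about 18% dropout rising with baseline in the intervention arm only, a baseline-adjusted complete-case estimate at T2 was −0.169 against a truth of −0.17. Only loss tied to change beyond what baseline and group explain remains a threat.
- A reader might infer that the check would look reassuring even if dropout explained the whole effect. That needs a one-arm delta of about 0.85 at 20% missing, and exact agreement is guaranteed only when losses precede T1.

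**Conclusion.** The point holds as a cheap improvement. The complete-case analysis is a weak and non-specific check: it can signal that dropout is not completely at random, but its agreement with the mixed model does not show robustness to dropout related to unobserved change in BMI-SDS. The primary estimator is not shown to be wrong.

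The possible bias is 0.02–0.04 BMI-SDS for a delta of 0.2 and 0.05–0.10 for a delta of 0.5, over the article's own attrition range. These figures rest on an assumed delta applied to one arm. If the same delta applied in both arms with equal missing fractions, the bias would cancel. The conclusion also assumes a likelihood fit to all available T1 and T2 values.

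**What to change.** In section 2.6.3, keep the complete-case analysis but call it a descriptive supplement, and add a prespecified sensitivity analysis for BMI-SDS:

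- State in section 2.6.2 that the mixed model uses all available T1 and T2 values and assumes missing at random, and say how missing baseline covariates are handled.
- Multiply impute missing T1 and T2 BMI-SDS under missing at random, using group, baseline BMI-SDS, the model covariates and any observed T1 or T2 value.
- Shift the imputed values by delta, first in the intervention arm alone and then in both arms, over a prespecified range up to the tipping point at which the conclusion changes.
- Report the tipping point and judge whether a delta of that size is credible, given the attrition seen in each school.

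This needs no new data. SAS 9.4 is already specified, and PROC MI with its MNAR statement does the shifting. The cost is a few extra runs, a paragraph of text and a delta range that must be justified in advance. It does nothing for the separate problem of one school per arm, where school and intervention effects cannot be told apart.
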